**Intervention acceptability**

At the end of the study, participants will report on a continuous rating scale of 0 to 100 if the intervention was acceptable for self-managing their bulge/PSH, with a higher score indicating that the intervention was extremely useful.

The acceptability of the intervention will also be explored at the end of the study through semi-structured face-to-face or telephone interviews (depending on participant preference) with participants. A semi-structured interview is chosen as it allows flexibility with sequencing of questions and for following up on any topics that arise naturally through discussion [49]. These interviews will last approximately 30 min and cover participants’ opinions on perceived challenges and barriers to being physically active, content of the intervention, and its perceived relevance and usefulness in self-managing bulge/PSH. These interviews will also be used to gather participants’ opinions of trial procedures.

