**Methods:**

Subjects and sample

There were approximately 20 adults with a bowel stoma and PSH. People with previous PSH repair will be excluded as well as people who already do core training.

Study design

This is a feasibility study of a randomised controlled trial with 2 months follow-up, in 2 sites using mixed methods. Stage 1 involves intervention development and in stage 2, intervention and trial parameters will be assessed.

Intervention

A theoretically informed physical activity intervention was done, targeting people with PSH.

Main outcome of feasibility study

The main outcome is the decision by an independent Study Steering Committee whether to proceed to a full randomised controlled trial of the intervention.

Other outcomes

We will evaluate 4 intervention parameters—fidelity, adherence, acceptability and safety and 3 trial parameters (eligible patients’ consent rate, acceptability of study design and data availability rates for following endpoints):
I.Diagnosis and classification of PSHII.Muscle activationIII.Body composition (BMI, waist circumference)IV.Patient reported outcomes: QoL, body image and physical functioningV.Physical activity;VI.Psychological determinants of physical activity

Other data

Included are other data such as interviews with all participants about the intervention and trial procedures.

Data analysis and statistical power

As this is a feasibility study, the quantitative data will be analysed using descriptive statistics. Audio-recorded qualitative data from interviews will be transcribed verbatim and analysed thematically.

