### Aims

The aim of this feasibility study is to evaluate 4 intervention parameters—fidelity, adherence, acceptability and safety and 3 trial parameters, namely eligible patients’ consent rate, acceptability of study design (i.e., randomised controlled trial), and data availability rates for measuring the following endpoints (i.e., mechanisms and outcomes (see Fig. 1)) pre- and post-intervention:
I.Diagnosis and classification of PSHII.Muscle activationIII.Body composition (BMI, waist circumference)IV.Patient reported outcomes: QoL, body image and physical functioningV.Physical activityVI.Psychological determinants of physical activity

The aim of the future trial is to determine whether a structured physical activity intervention that includes core training and signposting to written guidance about physical activity in people who have bowel stoma and have PSH improves outcomes in comparison with signposting to written guidance only.

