## Methods

### Project design

This is a feasibility study of a randomised controlled trial with 2 months follow-up, in 2 sites, with 20 participants, using mixed methods. Stage 1 involves intervention development and in stage 2, intervention and trial parameters will be assessed.

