**Acceptability of randomised controlled design**

Eligible patients’ consent rate and the retention rate for the study will be used as proxies for acceptability of a randomised controlled trial design. The retention rate is defined as the number of consenting participants who complete baseline and follow-up measures. Based on our previous study of a physical activity intervention for people with stoma [47], we estimate a 60% retention rate.

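### The 0–100 acceptability rating is anchored on usefulness, so the only numeric measure of intervention acceptability mixes two constructs; asked once at the end, it may also over-represent those who stay

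*Protocol article*

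**What the plan says.** The Aims section of the protocol article states: "The aim of this feasibility study is to evaluate 4 intervention parameters". These are fidelity, adherence, acceptability and safety.

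Under Intervention acceptability, two sources are described:

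- **A rating.** It is collected once, when the study ends, as a score between 0 and 100. The item is described as asking "if the intervention was acceptable for self-managing their bulge/PSH, with a higher score indicating that the intervention was extremely useful".
- **Interviews.** "The acceptability of the intervention will also be explored at the end of the study through semi-structured face-to-face or telephone interviews". The listed topics include barriers to activity, the content of the intervention, and how relevant and useful participants found it. The abstract (Methods, Other data) describes these as "interviews with all participants about the intervention and trial procedures".

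The project is described as a feasibility trial "with 20 participants, using mixed methods". On retention, the section Acceptability of randomised controlled design says "we estimate a 60% retention rate" and gives the definition: "The retention rate is defined as the number of consenting participants who complete baseline and follow-up measures".

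The Data analysis section says that intervention parameters will be reported overall and by site, that missing data for all outcomes will be summarised overall and by arm, and that the data will inform the decision on a full trial. The progression criteria themselves are in Table 1, which is not reproduced in the text available here.

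**The concern.** The question put to the participant and the meaning attached to the answer differ. Acceptability is about whether someone is willing to do what the intervention asks: weekly consultations, home exercise and a diary over 12 weeks. Usefulness is about whether they think it helped. The two can diverge in either direction. A participant may tolerate the programme well and notice no benefit, or see benefit and find the burden too great. A score of 50 could come from either person.

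The rating is also taken at a single time point, at the end. Adherence and discomfort are rated weekly, so someone who stops part-way leaves some data on those two parameters. The acceptability rating has no earlier reading to fall back on.

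At stake is the interpretation of one of four intervention parameters in a study whose purpose is to inform a decision on a full trial. Sample size, error rates and the figures stated in the protocol are not affected.

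**Working it through.** **1. Construct against anchor.** The plan states no figure that depends on this item, so there is nothing to reproduce. The check is to set the three participant-reported ratings of the intervention side by side.

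| Parameter | What is asked | What the stated end of the scale means | Match | When |
|---|---|---|---|---|
| Adherence | Success in completing the prescribed exercises | 10 = fully successful | Yes | Weekly |
| Safety | Discomfort and pain during the exercises | 0 = none | Yes | Weekly |
| Acceptability | Whether the intervention was acceptable for self-management | Higher = extremely useful | No | Once, at the end |

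Only the acceptability item has an anchor from a different construct. The meaning of a low score is not described.

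**2. Do the interviews repair it?** In part. They explore acceptability directly and cover barriers and content. They take place at the same stage as the rating, and their topics again include usefulness. They add information about acceptability but do not show what a given numeric score meant to the person who gave it.

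**3. How far could end-of-study timing matter?** This is a conditional illustration, not an estimate.

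Inputs:
- Total sample: 20 (Project design).
- Retention r: 0.60 (Acceptability of randomised controlled design).
- Allocation 1:1, so about 10 in the intervention arm. This is an assumption, since no ratio is stated.
- Only retained participants give the rating. This is an assumption that the text does not state.
- Gap between the mean ratings of those who stay and those who do not: assumed values of 0, 20, 30 and 40 points. None is in the document.

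Expected respondents: 20 × 0.60 = 12 overall; 10 × 0.60 = 6 in the intervention arm.

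Overstatement of the arm mean = (1 − r) × gap.

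| Assumed gap | r = 0.60 (plan) | r = 0.80 (for comparison) |
|---|---|---|
| 0 | 0.4 × 0 = 0 | 0.2 × 0 = 0 |
| 20 | 0.4 × 20 = 8 | 0.2 × 20 = 4 |
| 30 | 0.4 × 30 = 12 | 0.2 × 30 = 6 |
| 40 | 0.4 × 40 = 16 | 0.2 × 40 = 8 |

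Bounds with no assumption about the gap, for an illustrative observed mean of 80 at r = 0.60:
- non-respondents all at 0: 0.6 × 80 + 0.4 × 0 = 48;
- non-respondents all at 100: 0.6 × 80 + 0.4 × 100 = 88.

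If those who stop are also asked, the term (1 − r) refers only to people who give no rating at all, and it shrinks towards zero.

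**The case against.** Five arguments can be made in the plan's defence.

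- **The item does ask about acceptability.** It asks about acceptability for a purpose, self-management, and the interview topics treat usefulness as part of the same subject. A reader might infer that the score does not measure acceptability at all. The text does not support that: the score is confounded, not unrelated. Even if usefulness is one component of acceptability, an anchor that names only that component leaves the others, such as burden, without a place on the scale.
- **The item is paraphrased.** The adherence and discomfort questions are given verbatim, whereas this one is only described, so the questionnaire itself may be worded better. That is possible. In that case the correction is to the article's description, but the description as it stands is still mismatched.
- **Nobody is excluded.** A reader might infer that people who stop are left out. No text says so. The rating is asked of participants without restriction, the interviews are planned with all of them, and a telephone option exists. Retention is defined by completing baseline and follow-up measures, which differs from stopping the exercises or declining one rating. Someone may stop exercising and still be followed up. This objection stands. What remains is a risk, because the statement about all participants concerns the interviews and not the rating.
- **Missing data and early experience are partly covered.** The Data analysis section summarises missing data and reasons for non-availability, and the diary collects weekly free text on barriers. This also stands in part: it shows how many ratings are absent and gives some context, but it does not supply the absent ratings.
- **The score's role is unknown.** A reader might infer that the Steering Committee will decide on this number. With Table 1 not shown, it cannot be confirmed that the rating is a progression criterion or how it would be weighed against the interviews.

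**Conclusion.** The anchor mismatch holds and rests on a single sentence of the protocol article. The only quantitative measure of intervention acceptability mixes acceptability with perceived usefulness, and the interviews offset this only in part. The error could run in either direction and cannot be sized from the document.

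The timing point holds only as a risk. A single rating at the end, in a study expecting 60% retention, may over-represent those who stay. The 8 to 16 points shown above should not be read as an expected bias. They are 0.4 times assumed gaps and require that nobody outside the retained group gives a rating. The bias is zero if those who stop are also asked or would rate alike.

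This is a modest measurement point in a descriptive study. It is worth correcting because the remedy is cheap and acceptability is a named parameter of the study. The anchor point stands even if the timing point is set aside.

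**What to change.** 1. Anchor the existing item so that 0 means not at all acceptable and 100 means completely acceptable. If the questionnaire already does this, correct the description in the protocol.
2. Put usefulness for self-management in a separate 0–100 item with its own matching anchors.
3. State that both ratings are sought from everyone allocated to the intervention, including at the point when someone stops.
4. Report the number who answered out of the number allocated to the intervention beside each summary.

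The cost is one reworded item, one additional item for participants, and a brief contact with each person who stops. In an arm of about 10 (assuming equal allocation) that is a handful of contacts. The sample size and the rest of the analysis are unchanged.

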**Intervention safety**

There is no validated patient-reported or clinically relevant measure of discomfort or pain while exercising for people with PSH. Hence, a 10-point continuous rating scale that we have developed will be used to assess participants’ level of discomfort and pain while performing the prescribed exercises. Participants are advised of the potential for post-exercise pain and discomfort in the trial documentation. At the end of each week of the 12-week programme, participants will answer the following question:

‘On a scale of 0 to 10, how much discomfort and pain did you experience around your stoma and bulge/PSH when doing the prescribed exercises? A score of 0 indicates no discomfort or pain.’

Mean discomfort/pain scores for exercises over the 12-week period will be calculated. Adverse events (AEs) will be reported as part of the ethical conduct of the study as described below.

The topic of potential discomfort and pain while exercising will be discussed with participants at in-depth interviews. In addition, as a standard part of most consultations, participants will discuss how they have found the exercises in the previous week.

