#### What—procedures

The intervention will involve participants having 12 (1 per week) consultations with an exercise instructor. Professional associations for exercise specialists, such as the UK Chartered Institute for the Management of Sport and Physical Activity acknowledge that pre-exercise screening is an important part of the duties of an exercise specialist. Hence, the instructor will use the Physical Activity Readiness Questionnaire (PARQ) long version [42] so that she can prescribe an individualised exercise programme for each participant, taking account of medical history and current health status. Participants will be prescribed 4 different types of core training exercises with 4 levels of progression. These exercises are based on the Australian Physiotherapy and Pilates Institute methods programme [43]. Over the 12-week programme, there will be gradual progression in the prescribed frequency (number of times to perform the exercises that week), intensity (rate of exertion to perform the exercise that week) and duration (minutes to perform these exercises).

The exercises will conform with the new guidelines issued by the American College of Sports Medicine for people with an ostomy appliance [44]. Gradual progression also reduces the risk of participants over-exerting themselves with exercising and causing injury.

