#### Data analysis

Intervention parameters (fidelity, adherence, acceptability and safety) and trial parameters (eligible patients’ consent, retention and data availability rates) will be reported overall and by site. Reasons for non-fidelity, non-adherence, non-consent, non-randomisation, and non-availability of data will be summarised. Follow-up rates will be reported overall, by site and by arm to demonstrate the acceptability of the schedule for both arms. The analysis will focus on confidence interval estimation rather than formal hypothesis testing. All outcome measures will be summarised by arm, at each time point together with 95% confidence intervals. Levels of missing data for all outcomes will be summarised overall and by arm. AEs will be monitored and rates compared descriptively between study groups. Qualitative thematic analyses of audio-recorded interviews and focus groups will be conducted using the Framework approach [64]. These data will inform the decision to proceed to a Phase III trial (Table 1).

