### Safety reporting

The AE reporting procedures will follow those of NHS guidelines for research trials [66]. All participants will be advised and encouraged to report concerns to the research team, their stoma nurse and the clinical exercise instructor. All serious adverse events (SAE) and AEs will be recorded regardless of whether they are related to participation in the physical activity intervention and sent to the Chief Investigator who will use the NHS recommended form [66] to report the SAE to the Research and Ethical Committee that approved the study.

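### The 12-week mean pain score can hide severe weeks or severely affected participants, and unequal contact leaves the between-arm adverse event comparison open to ascertainment bias

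*Protocol article*

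**What the plan says.** **Pain score.** The Intervention safety section of the protocol article has participants answer a 0 to 10 item at the end of each of the 12 weeks: "how much discomfort and pain did you experience around your stoma and bulge/PSH when doing the prescribed exercises". The only numerical summary named is this: "Mean discomfort/pain scores for exercises over the 12-week period will be calculated". The article does not say whether weekly scores are pooled or first averaged within each participant, or how weeks without exercise are treated.

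**Other safety information.** The same section keeps adverse events apart from the score: "Adverse events (AEs) will be reported as part of the ethical conduct of the study as described below". Pain is also a topic at the interviews, and "as a standard part of most consultations, participants will discuss how they have found the exercises in the previous week". Under Safety reporting, all adverse events and serious adverse events "will be recorded regardless of whether they are related to participation in the physical activity intervention". The reporting route is stated as follows: "All participants will be advised and encouraged to report concerns to the research team, their stoma nurse and the clinical exercise instructor".

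**Comparison.** Under Data analysis: "AEs will be monitored and rates compared descriptively between study groups".

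**Contact by arm.** Under What—procedures: "The intervention will involve participants having 12 (1 per week) consultations with an exercise instructor". Intervention fidelity expects a mean of about 10. Under Intervention and comparator group, the control arm is only signposted to charity guidance.

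**The concern.** Safety is one of the four intervention parameters listed under Aims, and Data analysis says the results inform the decision on a full trial. Two features of the stated methods weaken what the Study Steering Committee would see.

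First, tolerability of exercise is a question about the worst weeks and the worst-affected people, and a mean is insensitive to both. Because the item is conditional on exercising, someone who stops because of pain has nothing further to score. The weeks most relevant to safety may then carry little weight.

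Second, events of any cause count, but the arms differ in how often anyone is in touch with the participant. One of the three named recipients of reports, the exercise instructor, is described as consulting only with the intervention arm. More events could therefore be recorded there with no true difference in risk. The two weaknesses may pull in opposite directions: the pain mean can reassure too readily, while the event comparison can alarm without cause.

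**Working it through.** The article gives no safety event rate, detection probability or target precision, so there is no stated figure to reproduce. All scores and capture probabilities below are assumptions for illustration. About 10 per arm is also assumed: the total of 20 is stated, the allocation ratio is not.

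**1. Dilution by averaging**
- One participant, one week at 8 and eleven at 1: (8 + 11 × 1)/12 = 1.58. The maximum is 8.
- Arm of 10, one participant at 10 every week and nine at 1: (10 + 9 × 1)/10 = 1.9.

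**2. Dependence on aggregation and on weeks without exercise**

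Take an arm of 10. Four people score 8 in weeks 1 and 2 and then stop; six score 1 for all 12 weeks.
- Pooled weekly scores, unscored weeks missing: (4 × 2 × 8 + 6 × 12 × 1)/(8 + 72) = 136/80 = 1.7.
- Mean of participant means, unscored weeks missing: (4 × 8 + 6 × 1)/10 = 3.8.
- Unscored weeks counted as 0: 136/120 = 1.13 by either route.

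The same data give 1.1, 1.7 or 3.8. None of the three shows that four of ten stopped after scoring 8.

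For a single person scoring 8 for three weeks and then stopping, the mean is 24/12 = 2.0 with later weeks as 0, and 8.0 with them missing.

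**3. Unequal ascertainment**

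Observed proportion = true proportion × probability of capture. With the same true proportion in both arms it cancels, so the apparent risk ratio is the ratio of capture probabilities. With 0.9 assumed in the intervention arm:

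| Control capture | Apparent ratio |
|---|---|
| 0.3 | 3.0 |
| 0.5 | 1.8 |
| 0.6 | 1.5 |
| 0.7 | 1.29 |
| 0.9 | 1.0 |

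As an alternative, suppose each contact captures an event with probability q, so that capture over k contacts is 1 − (1 − q)^k. For q from 0.1 to 0.3, 10 contacts capture 65% to 97% and 2 contacts capture 19% to 51%.

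**4. Precision**

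The Wald 95% half-width for a risk difference with 10 against 10 is 1.96 × √(2p(1 − p)/10). This is 0.35 at p = 0.2, 0.40 at p = 0.3 and 0.44 at p = 0.5. For 0 events in 10, the exact two-sided 95% upper limit is 1 − 0.025^(1/10) = 31%.

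For comparison, with a true proportion of 0.3 and capture of 0.9 against 0.5, the spurious difference is 0.27 − 0.15 = 0.12, well inside the half-width.

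**The case against.** **Harm is reported in other ways.** A reader might infer that harm as a whole is averaged away. The article does not support that. Adverse events and serious adverse events are recorded individually whatever their cause, interviews and most consultations cover how the exercises went, and the diary has a free-text field for barriers. Data analysis also promises a summary of reasons for non-adherence and of missing data, so people who stop in pain should be visible there. This stands, and it confines the first point to the pain score.

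**Aggregation may belong to the analysis plan.** Pooling and the handling of unscored weeks are details an unseen plan may settle, and the low figure of 1.7 arises only under pooling. That is fair, and the absence of those rules is not the complaint. The point is that the summary the article does fix is a mean, and no version of it shows the worst week or the worst-affected person.

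**Bias in the event comparison is not demonstrated.** The article does not say that adverse events are formally solicited at consultations. Controls meet a researcher at baseline and follow-up, all participants are interviewed, and the cited NHS procedures or the full protocol may prescribe a common enquiry. The capture probabilities are assumed, and equal capture gives a ratio of 1.0. This too stands: the risk is credible, its size unknown. The comparison is also descriptive in about 20 people, so imprecision limits it at least as much.

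**A comparison resting solely on a follow-up question would have its own flaw.** Expected retention is 60%, about 12 of 20, so people who left because of harm could be missed. The fix allows for this.

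**Conclusion.** The point holds in a limited form. The one stated numerical summary of the pain score can hide a severe week or a severely affected participant, and its value can move from 1.1 to 3.8 on the same illustrative data according to choices the article does not state. The descriptive adverse event comparison is open to ascertainment bias, probably against the intervention, because weekly consultations and described instructor contact exist in one arm only. The apparent ratios of 1.5 to 3.0 rest entirely on assumed capture of 90% against 30% to 60%.

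A reader might go further and conclude that the comparison is biased, or that a rule based on mean pain will distort the progression decision. Neither can be established. The design facts are clear but the amount of differential capture is not, and the progression criteria in Table 1 are not shown, so whether the mean pain score decides anything cannot be checked. The changes are worth making because they improve on stated methods at very little cost.

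**What to change.** **1. Pain score.** Keep the mean, and report beside it:
- each participant's maximum weekly score;
- the number and proportion with any week at or above a level that the study team chooses in advance;
- scores by week, with the number contributing;
- the number who stopped or modified the exercises because of pain, drawn from the reasons for non-adherence already to be summarised.

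Do not count weeks without exercise as zero, and state whether the mean is over weekly scores or over participants.

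**2. Adverse events.** Ask both arms the same structured question at the planned follow-up contact, and attempt it also in those who stopped or withdrew. Show the between-arm comparison on that common question with the number answering in each arm. Present all recorded events by arm and by source (volunteered, consultation or diary, common question), and qualify the all-source comparison for unequal contact.

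**Cost.** Part 1 is extra tabulation of data already to be collected. Part 2 adds one question at an existing contact and an attempt to reach those who left. The drawbacks are longer recall and non-response on the common question, which is why the all-source listing is kept beside it.
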